**Figure 1 F1:**
[figure not shown]
The PainDrawing application allows registering individual pain levels using the Visual Analogue Scale and a standardised pain drawing for pain location and characteristics.

#### Exposure to impacts

A data logger system (MAREC, Research Electronics AB, Siljansnäs, Sweden) was designed specifically for this study. The device comprises three triaxial micro-electromechanical system (MEMS) accelerometers with a range of ±25*g*, a Global Positioning System antenna for tracking speed, and a data logger unit with 10 digital channels (figure 2). The acceleration data are recorded at a sampling rate of 600 Hz and stored on an internal removable 16 GB USB memory stick. One accelerometer fitted to the hull will record hull accelerations. Two accelerometers fitted in kidney belts, as depicted in figure 2, will be worn by two operators, normally the coxswain and the navigator.^11^

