## Introduction

 High-speed boat operations expose humans to slamming-induced impacts, where the boat hull hits the waves, transmitting significant impact forces through the boat to its occupants. The intensity and frequency of slamming impacts depend on a variety of factors, including the speed of the boat, the sea state and the design of the boat.^1^ Musculoskeletal injuries sustained during high-speed boat operations are typically caused by repeated exposure to whole-body impacts.^1 2^ The induced forces can bend, twist and compress the spine, causing vertebral fractures, disc herniations and distortion injuries. Slamming can also cause significant impact forces transmitted through the upper extremities, leading to injuries such as rotator cuff tears and wrist fractures.^3^ Moreover, these forces may affect the brain, leading to neurological symptoms and injuries, including cognitive effects and mild traumatic brain injury.^4^

Several studies have evaluated the effects of impact exposure on operator performance during high-speed boat transits.^5^ Post-transit, operators were found to have decreased running performance,^6^ increased inflammation as reflected by salivary cortisol^7^ and increased muscle damage as reflected by elevated levels of creatine kinase.^8^ Impaired cognitive functionality affecting operational readiness, even unconsciousness, has been reported.^1^ A recently published systematic review identified five scientific reports describing 3312 injuries sustained during 3467 person-years onboard high-speed boats.

Repetitive exposure to slamming may lead to chronic musculoskeletal disorders, pain conditions and disabilities. Long-term exposure to whole-body vibration is known to have detrimental cumulative effects on the intervertebral discs and increases the incidence of low-back pain.^9 10^ Additionally, slamming impacts can cause musculoskeletal injuries, particularly to the spine and lower extremities.^13 5 11^,^14^ To address the occurrence of these injuries, legal exposure regulations are in place, and operational restrictions have been implemented.^15^ However, littoral and amphibious operations often require rapid transits to transport operators, irrespective of weather conditions and sea states.

There are several reasons why human impact exposure onboard high-speed boats needs to be studied.

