*Injury prevention*: researchers can identify effective strategies to prevent or mitigate injuries by examining the nature and severity of slamming impacts and their correlation to reported pain and risk of musculoskeletal injuries due to repeated exposure.^116^,^18^*Health and safety regulations*: understanding the nature and magnitude of impact exposure that may cause injuries can guide the development of relevant health and safety regulations for high-speed boat operations and help avoid unwarranted operational restrictions.^19^*Boat design and technology*: by studying impact exposure, researchers can identify areas for improved boat design and technology.^20^ For example, by developing better shock-absorbing materials or hull shapes, naval architects can help reduce the exposure to impact on the human body.*Training*: exposure to high, potentially harmful magnitudes of whole-body impacts has not been shown to have positive training effects. Knowing what magnitudes of exposure are sustainable can improve training routines and objectives.*Operational optimisation*: the slamming-induced impacts can also affect the performance of high-speed boats.^21^ By studying the nature and severity of slamming impacts, researchers can identify ways to optimise boat performance, such as adjusting speed or altering course in response to changing sea conditions. With a better understanding, operators can make better decisions, improving operational efficiency.

This prospective, multicentre, observational, cohort study on human impact exposure onboard high-speed boats aims to determine (1) the nature and the magnitudes of slamming-induced impacts on humans onboard and (2) the types and magnitudes of impacts that are potentially harmful.

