### Outcomes, data sources and measurements

#### Pain

Pain is a common symptom experienced by high-speed boat operators exposed to repeated slamming impacts, and it is a common reason that operators seek medical attention or modify their work activities.^1^ By studying the occurrence and duration of pain and its correlation in time after slamming-induced impacts, the study aims to assess the risks of injurious exposure. Pain can be monitored non-invasively using validated methods, such as the Visual Analogue Scale (VAS) or Numeric Rating Scale, which rate pain intensity, and pain drawings to assess pain location, duration and interference with activities.

In this study, self-reported pain will be logged daily through a smartphone application, PainDrawing (figure 1),^23^ adapted specifically for this project.^24^ The application is based on the Nordic Minister Council’s pain drawing form and a VAS. PainDrawing can be downloaded freely from Google Play and Apple AppStore and works offline and in flight mode. Reported pain data will comprise the following characteristics: location, pain modality, intensity and duration. Participants will be urged to log pain daily for the whole test period, regardless of whether they have been on board a boat or not. Participants will serve as their own controls by comparing periods of exposure onboard with periods of not working onboard.

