### Statistical methods

We will report descriptive statistics and calculate the mean, SD and range for human impact exposure and pain scores. Peak acceleration values, m/s^2^, will be registered in all three axes, x, y and z. A data analysis engine will categorise impacts with various combinations of the impact characteristics and allow for calculating correlations to registered pain experiences and various variables of the reported pain. We will use Pearson correlation coefficients to examine the association between human impact exposure and pain scores. We will also use linear regression to examine these associations while controlling for potential confounding variables (eg, age, sex, body mass index). Multivariate analysis based on analysis of variance (ANOVA) and logit models will be used to identify which characteristics of the impacts correlate to reported pain of various intensities, locations and durations after exposure. The results of the statistical analysis are expected to indicate which impact characteristics show a correlation to reported experiences of pain. Based on these findings, we will establish which impact exposure levels and characteristics are safe regarding physical and cognitive capabilities.

This analysis can also validate alternative ways of quantifying human exposure to discrete whole-body impacts and their potential relevance for predicting the risk of injury. Candidates for alternative units include calculated kinetic energy transferred or absorbed, J/kg, and the speed of this transfer, mechanical power, J/(kg·s). The analysis may need to include the calculated total change of speed and the distance during which the retardation of the boats and the human bodies occurs in each impact.

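### If coxswains ease off when in pain, exposure on onboard days partly reflects pain already present, and the listed analyses would shrink the acute exposure-pain slope towards no harm by an unknown amount

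*Protocol article*

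**What the plan says.** All references are to the protocol article.

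- **Exposure to impacts.** One sensor is on the hull. The two body-worn sensors "will be worn by two operators, normally the coxswain and the navigator".
- **Introduction.** Slamming intensity and frequency "depend on a variety of factors, including the speed of the boat, the sea state and the design of the boat". Under operational optimisation, the examples of what can be changed under way include "adjusting speed or altering course in response to changing sea conditions". The same section notes that "littoral and amphibious operations often require rapid transits to transport operators, irrespective of weather conditions and sea states".
- **Pain.** Of pain in this population: "it is a common reason that operators seek medical attention or modify their work activities". Pain is logged daily, on boat days and other days alike. Each participant's onboard periods are compared with that participant's periods off the boat.
- **Statistical methods.** The first association measure is a Pearson correlation of exposure with pain, with no adjustment. Then: "We will also use linear regression to examine these associations while controlling for potential confounding variables (eg, age, sex, body mass index"). ANOVA and logit models follow. The section ends by saying that the results will establish which exposure levels are safe.
- **Risk of bias, confounding factors and compliance.** The confounders named are injuries from other activities and pathology present at baseline. There is a general commitment to adjust for potential confounders. Current pain as a cause of exposure is not mentioned.

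**The concern.** The planned models treat exposure as something that happens to the participant. For whoever is steering, it may be partly chosen. A coxswain who starts the day in pain and drives more gently contributes a day with low impact and high pain. A coxswain without pain who drives hard contributes the opposite. Both pull the pain-on-exposure slope down.

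Scoring pain after the transit does not remove this, because pain present beforehand persists into the later score. The example covariates are in effect fixed over a 90-day follow-up, so they cannot absorb a day-to-day feedback. The own-control contrast compares days on the boat with days off it. It does not address the slope among onboard days.

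The direction matters because of how the results will be used. Safe levels are to be read from these associations, and the Discussion would use them to suggest limits for exposure in training. A slope that is too small makes harmful levels look tolerable.

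**Working it through.** The article gives no figure for this feedback, so there is none to reproduce. Every value below is an assumption except the 20 mm SD. That comes from Target sample size, where it is the SD for back pain VAS. Using it as the SD of pre-transit pain is itself an assumption, so 10 mm is shown as well.

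**Closed form, onboard days only**

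Let E be exposure standardised to SD 1, P0 the pain before the transit with SD σ, and the correlation of E with P0 equal to -g. Let pain after the transit be

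Y = ρ·P0 + 3·E + error,

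with a true effect of 3 mm per SD of exposure and carry-over ρ = 0.5. The unadjusted slope is

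Cov(E, Y) / Var(E) = 3 - ρ·σ·g.

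The pooled slope averages this equally with a navigator slope of 3, assuming that the navigator's own pain does not alter the boat's speed.

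| σ (mm) | g | Coxswain slope | Pooled slope |
|---|---|---|---|
| 20 | 0.1 | 3 - 1.0 = 2.0 | 2.5 |
| 20 | 0.2 | 3 - 2.0 = 1.0 | 2.0 |
| 20 | 0.3 | 3 - 3.0 = 0.0 | 1.5 |
| 10 | 0.1 | 3 - 0.5 = 2.5 | 2.75 |
| 10 | 0.2 | 3 - 1.0 = 2.0 | 2.5 |
| 10 | 0.3 | 3 - 1.5 = 1.5 | 2.25 |

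A simulation of 400,000 onboard days with σ = 20 gave coxswain slopes of 2.01, 1.04 and -0.03 unadjusted, and 3.00, 3.02 and 2.97 with P0 in the model. The full recovery is built in, because the simulated confounder is exactly the covariate added.

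**Second model, day by day**

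This used 96 boats over 90 days, exposure shared by coxswain and navigator, and a true slope of 0.20. Exposure is lowered by k times the coxswain's last logged pain (k is a coefficient, not a correlation).

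| k | Coxswain, raw | Coxswain, within person | Coxswain, within person plus prior-day pain | Navigator, raw | Both pooled, raw |
|---|---|---|---|---|---|
| 0 | 0.20 | 0.20 | 0.20 | 0.20 | 0.20 |
| 0.1 | 0.12 | 0.17 | 0.20 | 0.20 | 0.16 |
| 0.2 | 0.06 | 0.15 | 0.20 | 0.20 | 0.13 |
| 0.3 | -0.01 | 0.12 | 0.20 | 0.20 | 0.10 |
| 0.5 | -0.09 | 0.08 | 0.20 | 0.20 | 0.05 |

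If the feedback instead runs through pain felt on the day but not logged before the trip, with coefficients 0.1, 0.2 and 0.3, the within-person model with prior-day pain gives 0.17, 0.14 and 0.11. The correction is then only partial.

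Both models agree on direction. The bias falls on the coxswain, and pooling dilutes it.

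**The case against.** The strongest objection is that the central link is inferred. No sentence says that the coxswain sets the speed, or that anyone slows the boat because of pain. The remark on adjusting speed concerns sea conditions and boat performance. Modifying work activities could equally mean changed duties or staying ashore. Required rapid transits also leave less room for choice. All of this stands, so the point is conditional.

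Second, the covariates are only examples, the bias section promises adjustment for confounders, and the article disclaims causal conclusions. Prior pain is therefore not excluded, and an analysis plan that is not shown may include it. That is fair, and it keeps the point modest. It does not dispose of it. The leading measure is stated to be an unadjusted correlation, and the confounders named do not include one that varies daily and is itself the outcome. A disclaimer on causality also sits badly with reading safe levels from the slope.

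Third, the planned subgroups (for example operators against passengers) could accommodate a split by role. They could, but coxswain and navigator are both called operators, so the example given does not separate them.

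A reader might infer that a real effect would be cancelled or reversed. The documents do not support that. In the closed form the coxswain slope reaches zero only at the most extreme setting, and the simulated -0.03 there is noise. In the second model only the coxswain's raw slope passes below zero, at feedback strengths for which the documents give no evidence. The pooled raw slopes and the coxswain's within-person slopes shrink but stay positive for every value of k shown.

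**Conclusion.** The point holds as a conditional bias. If coxswains ease off when in pain, the analyses listed in Statistical methods would understate the acute exposure-pain slope. The documents support the ingredients (sensor placement, the role of speed, pain changing work behaviour) but not the behaviour itself or its strength.

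Under the assumptions in the closed form, a true +3 mm per SD becomes 0 to 2.5 mm for coxswains and 1.5 to 2.75 mm pooled half and half with navigators. These ranges illustrate what could happen and do not estimate what will. Attenuation is the supported conclusion; cancellation or reversal of the study's overall association is not. The change is worth making because it is cheap and the bias runs in the unsafe direction.

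**What to change.** 1. In the models of acute pain after a transit, include the participant's last pain score logged before that transit. Keep the model without it alongside and report both.
2. As a sensitivity analysis, estimate the exposure slope separately for the crew member steering and for other crew. Do not add a rule that discards the steering crew when the slopes differ, since the roles may also differ in real susceptibility.
3. Record who steered on each trip. The article says only who normally wears the sensors. Inclusion is expected to run until mid-2027, so this can still be added.
4. State the possible feedback from pain to exposure among the limitations.

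The first step uses the existing daily log, provided that entries can be ordered in time against the transit. Otherwise the previous day's score serves.

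The costs should be stated. Prior pain may itself carry the effect of earlier slamming, so the adjusted slope is the acute effect and not the cumulative one, which is why the unadjusted model is kept. Correction is only partial if unlogged same-day pain drives the feedback. Role-specific slopes are less precise than a pooled one, and recording the steering role is a small extra item of data collection.

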**Figure 2 F2:**
[figure not shown]
On the left is a photograph of the MAREC device and related connections and on the right the kidney belt containing a three-axis accelerometer worn by the participating operators.

Accelerations will be analysed on all nine channels for the following characteristics:

*Number of impacts*: slamming impacts will be defined by the amplitude of the vertical accelerations measured on the boat hulls, where this peak acceleration exceeds 20 m/s^2^ or 2*g*. Peak accelerations below this level will not qualify as impacts relevant for analysis in this study.*Peak acceleration levels*: the peak acceleration value will be defined as the highest registered acceleration data point in each impact.*Range of rise times and correlation to peak acceleration levels*: rise time is defined as the time from nominal 0*g* to peak acceleration value.*Range of vector sum*: the force vectors will be the calculated vector sum resulting from the vertical force vector Z and the two horizontal force vectors X and Y. This value will be higher than any of the included three single-axis values and will show the magnitude of the total impact.*Three-dimensional impact measurement*: the direction and the acceleration of each impact will be recorded on the hull and on two boat operators per boat, using three-axis accelerometers.*Range of impact durations*: impact durations will be calculated as the time from the datapoint where the vertical acceleration exceeds 0*g* in each hull impact, exceeding 2*g* vertically until the last datapoint falls under 1.0*g*.*Range of jerk (speed of onset of impacts)*: the range of jerk, defined as the rate of the initial change of acceleration, will also be analysed. It is the derivative of the peak acceleration value (m/s^2^) divided by the time it took to reach it.^25^

Data output from the device will be presented in various graphic formats, for example, line graphs, allowing zooming from one full day of exposure down to showing the shape of a single impact regarding all characteristics of the impact (figure 3), or as histograms showing the numbers of impacts reaching different peak levels.^26^ To allow for a wide variety of analyses, all acceleration data will be stored in binary files as unfiltered raw data (figure 4). If a participating centre cannot use the MAREC data logger, another device with identical performance, sensors, software and output file format may be used.

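### Only events with a vertical hull peak above 2 g are analysed, so the plan cannot support safe-level conclusions for lower, mainly horizontal or body-amplified events outside that gate

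*Protocol article*

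**What the plan says.** All references are to the protocol article.

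- **Which events exist.** Under Exposure to impacts (characteristics listed after Figure 2), "slamming impacts will be defined by the amplitude of the vertical accelerations measured on the boat hulls". To count, the peak must lie above a level given as 20 m/s² or 2 g. Smaller peaks are then set aside: "Peak accelerations below this level will not qualify as impacts relevant for analysis in this study". The definition of impact duration repeats the vertical hull condition.
- **What is measured on them.** The same list begins "Accelerations will be analysed on all nine channels for the following characteristics". It includes "the calculated vector sum resulting from the vertical force vector Z and the two horizontal force vectors X and Y", and says that "the direction and the acceleration of each impact will be recorded on the hull and on two boat operators per boat".
- **What is stored.** All acceleration data are kept as unfiltered raw files so that varied analyses remain possible.
- **The aim.** The second aim in the Introduction is to determine "2) the types and magnitudes of impacts that are potentially harmful". On mechanism, the Introduction says: "The induced forces can bend, twist and compress the spine, causing vertebral fractures, disc herniations and distortion injuries". It attributes the typical injuries to repeated whole-body impacts.
- **The planned conclusion.** Statistical methods says that the study will establish which exposure levels and characteristics are safe. The Discussion looks ahead to suggested exposure limits for training and to calibrated dashboard warnings.

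The article gives no reason for the 2 g level and describes no analysis at another level or with another trigger.

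**The concern.** One channel of nine decides whether an event is analysed at all. Three kinds of event fall outside by rule: slamming with a vertical hull peak at or below 2 g, events that are mainly horizontal, and any event that is stronger at the operator than at the hull but stays under the gate there. The article itself regards the vector sum as the measure of total impact and puts sensors on two operators, yet neither plays a part in detection.

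What is at stake is the reach of the conclusions. A study that looks only above a fixed floor on one axis can rank harm above that floor. It has no analysed data from which to call anything below the floor, or in another direction, safe or harmful. If the results become training limits, silence about excluded events could be read as evidence that they are harmless.

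The number of impacts is a listed exposure variable. In a model that uses that count, an onboard day with only excluded events would, by definition, have a count of zero.

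**Working it through.** **Inputs from the document.** Gate: vertical hull peak above 20 m/s² or 2 g (Exposure to impacts). g = 9.81 m/s² (Figure 3 caption). Three triaxial sensors, one on the hull and two on operators (Exposure to impacts). Vector sum of the Z, X and Y components (same list).

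**1. The stated cut-off.** 2 × 9.81 = 19.62 m/s², and 20 / 9.81 = 2.04 g. The two values agree to rounding, but an event-detection rule needs one of them.

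**2. Channels.** 3 sensors × 3 axes = 9. One channel is the gate. The other 8 are two horizontal hull channels and six body-worn channels, and they are read only for events that pass.

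**3. Does the gate order events by total magnitude?** The component values below are illustrative and assume that the axis peaks coincide. Vector sum = √(vertical² + lateral²).

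| Vertical (g) | Lateral (g) | Vector sum (g) | Analysed? |
|---|---|---|---|
| 1.9 | 2.0 | √(3.61 + 4.00) = 2.76 | no |
| 1.0 | 4.0 | √(1.00 + 16.00) = 4.12 | no |
| 2.05 | 0 | 2.05 | yes |
| 2.1 | 0.2 | √(4.41 + 0.04) = 2.11 | yes |

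The excluded events in the table are larger in total than those kept.

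**4. Does this depend on gravity?** The article does not say whether the vertical reading includes static gravity. If it does, take 1 g off the vertical component. The first excluded event becomes √(0.9² + 2.0²) = √4.81 = 2.19 g, and the kept event becomes 1.05 g. The ordering is unchanged.

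**5. Body-worn sensors.** The documents give no hull-to-body ratio. If the body peak were 1.0, 1.25, 1.5 or 2 times the hull peak (assumption), a hull peak of 1.9 g would give 1.9, 2.4, 2.9 or 3.8 g at the operator. The event would be excluded in every case.

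**6. How many events are affected?** This cannot be computed. The article gives no distribution of peaks, directions or hull-to-body ratios, and any percentage would only restate an assumed distribution.

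**7. Rule against conclusion.** The aim covers types and magnitudes without a lower limit or a direction. The planned statement on safety is equally unrestricted. The analysed events are restricted on both.

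**The case against.** - **A threshold is needed, and a hull trigger is natural.** The Introduction describes slamming as the hull striking waves, and the dashboard device in the Discussion would use a hull accelerometer. This stands, and is a good reason to keep the rule as the main definition.
- **Horizontal and body-level data are analysed.** This is true for every event that passes. Direction, vector sum, rise time, duration and jerk can all be related to pain above the gate. A reader might infer that the study cannot answer its second aim, but the text does not support that: the aim is narrowed, not lost.
- **Excluded events need not be coded as no exposure.** A reader might infer that pain after them is credited to an unexposed reference and flattens the exposure-pain relation. The article does not say this. Its self-controlled comparison, under Pain, sets periods onboard against periods not working onboard, so a day of low-level slamming remains an onboard day. The zero count arises only in models built on the number of impacts.
- **Nothing shows that excluded events injure.** This also stands. The Introduction gives no injury level, does not tie bending or twisting to horizontal hull acceleration, and does not document body amplification below the gate. But a plan that intends to declare levels safe needs data on those levels, and absence of evidence does not supply them.
- **The study is exploratory, raw data are kept, and an analysis plan not shown may add other triggers.** This partly stands. Storage makes the remedy cheap, and Statistical methods foresees alternative exposure units for discrete impacts. But the article states outright that smaller peaks are not relevant for analysis. The point concerns that stated rule, not a missing detail.
- **20 m/s² against 2 g is rounding.** Agreed. One value should be stated, and nothing more hangs on it.

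**Conclusion.** The point holds as a limit on scope. As written, detection rests on one axis of one sensor, and the rule can exclude events with a larger vector sum than events it keeps (2.76 g against 2.05 g in the example). This restricts the second aim. It leaves the promised statement on safe levels and characteristics, and the training limits that would follow, without support for the excluded magnitudes and directions.

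Comparisons among events above the gate are not affected, nor is the contrast between onboard and off-board periods. The ordering example rests on illustrative components with coincident peaks, and body amplification is hypothetical. The share of events lost, and hence the size of any bias, is unknown. The change is worth making because it is cheap and the planned conclusion is broad.

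**What to change.** 1. Keep the vertical hull rule as the main definition. Give one numerical value for it, and state whether the vertical signal includes static gravity and what counts as zero.
2. Using the stored raw data, add prespecified sensitivity analyses of the exposure-pain relation with:
   - a vector-sum trigger at the hull or at either body-worn sensor; and
   - a detection level below the present gate, a daily cumulative dose computed without a threshold, or both. The lower level must be set against the declared zero. If the sensor reads 1 g at rest, a level described as 1 g above rest is the present gate and would add nothing.
3. Add to Statistical methods that no safety conclusion is drawn for magnitudes or directions that the detection rule excludes, and carry the same limit into the training-limit statement in the Discussion.

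No data need to be collected again. The cost is analysis time and a larger number of low-level events and artefacts to screen.
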